### Data management and statistical analyses

#### Statistical analysis plan

The sample size is based on previous EEG studies of similar design,^23 25^ but all analyses are exploratory, as to our knowledge so far no such study has been conducted during pregnancy or the post partum period. Statistical analyses will be performed with STATA V.15.1 (2017) and MATLAB V.9.5 (R2018b). Processing of the EEG data will be performed using Cartool software and statistical software.^52^ Demographic and other descriptive variables will be represented as means and SD or percentages where appropriate. Analysis of variance, t-tests or χ^2^ tests will be used to determine group differences between responses to food and non-food pictures, different food categories, brain responses between pregnancy and post partum states, between women with and without GDM and between normal weight and overweight/obese women. Regression analyses will be used to model the relationships between predictor variables and outcomes (such as between brain responses to food viewing with intuitive eating and metabolic health such as weight, body fat and glucose control). In the second step, we will investigate the impact of covariates, where appropriate, such as maternal age, gestational age and prepregnancy BMI on outcomes and adjust for them if necessary.

Twenty women with valid data for the primary endpoint in each group (n=40) will be investigated during pregnancy and at 6 months postpartum. In order to achieve this, we had to include more patients.

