### Aims of the present study

The overall aim of this observational study is to investigate brain responses to viewing pictures of foods of different fat and carbohydrate contents in women during pregnancy and in the post partum and their relationship with eating behaviour and metabolic health. We will investigate this in healthy women and in a metabolic high-risk group, that is, women with GDM to include a wide spectrum of metabolic health.

The main objectives are as follows:

Objective 1: To investigate differences in brain responses to food pictures of varying fat and carbohydrate content (HIGH-FAT/LOW-CARB; HIGH-FAT/HIGH-CARB; LOW-FAT/LOW-CARB; LOW-FAT/HIGH-CARB) during and after pregnancy, in women with and without GDM.

Objective 2: To investigate the cross-sectional and longitudinal relationships between brain responses to food viewing with reported food cravings, eating behaviour and metabolic health outcomes such as weight, body fat and glucose control during pregnancy and in the post partum.

Objective 3: To investigate differences in brain responses to food pictures in relationship to different emotional states and stress levels.

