### Study population, inclusion and exclusion criteria, and recruitment

We will include 40 women with valid data for the primary outcomes (20 women with GDM and 20 healthy controls) at both time points. In the initial tests, the EEG data of 14 women with GDM and 13 healthy controls were not valid (ie, too much noise, low quality of signal), which has been corrected since. We will therefore recruit at least 35 women with GDM and at least 34 healthy controls, in their 24–36 weeks of pregnancy, during their antenatal appointments visits at a Swiss University Hospital. GDM women (clinical group) will be recruited at the GDM clinic whereas healthy pregnant women without GDM (control group) will be recruited at the hospital’s ambulatory clinic.

For women with GDM, inclusion criteria are: gestational age 24–36 weeks, age ≥18 years, GDM diagnosed at 24–32 gestational weeks according to IADPSG and ADA criteria.^49 50^ For healthy controls, inclusion criteria include women with normal weight (prepregnancy BMI <25 kg/m2), with no prior or current GDM, no diets and weight changes above 5 kg in the last 5 years (except for pregnancy), no excessive pregnancy weight changes (less than twice of the Institute of Medicine recommendations).^51^ Women in both groups should be able to fluently speak and write either French or English.

Exclusion criteria include: pre-existing diabetes, eating disorders (Anorexia Nervosa, Bulimia Nervosa and Binge-Eating Disorder), vegetarian/vegan diet, uncontrollable nausea and vomiting, current insulin treatment, participation in an intervention study, current medication to treat psychiatric disorders, active suicidal thoughts.

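### The planned two-class weight comparison discards graded BMI information if the relation is roughly linear, and as written it also mixes weight class with GDM status

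*Protocol article*

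**What the plan says.** The Statistical analysis plan section names ANOVA, t-tests or chi-square tests, and says these "tests will be used to determine group differences between responses to food and non-food pictures", among food categories, between the two visits, and "between women with and without GDM and between normal weight and overweight/obese women". No BMI cut-off is given there. The only definition of normal weight is in the section on study population and recruitment, where for healthy controls "inclusion criteria include women with normal weight (prepregnancy BMI <25 kg/m2").

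The same section fixes the numbers: "We will include 40 women with valid data for the primary outcomes (20 women with GDM and 20 healthy controls"). The GDM inclusion criteria set no BMI limit.

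Two other uses of body size are planned in the analysis section. First, "Regression analyses will be used to model the relationships between predictor variables and outcomes", with weight, body fat and glucose control as examples of metabolic health. Second, a later step examines the impact of "maternal age, gestational age and prepregnancy BMI on outcomes and adjust for them if necessary". The form in which BMI would enter as a covariate is not stated.

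The Aims section explains why a high-risk group is studied: "that is, women with GDM to include a wide spectrum of metabolic health". All analyses are declared exploratory. No alpha, effect size, power target or BMI distribution is given.

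**The concern.** Prepregnancy BMI has to be known as a number to decide control eligibility and to serve as a covariate. The plan nevertheless tests it against brain response in two classes and gives no reason for doing so. A woman at 25.5 and one at 38 count as the same, while women at 24.5 and 25.5 count as opposites. That sits badly with the aim of covering a spectrum of metabolic health, and 40 women leave little information to spare.

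The eligibility rules add a second difficulty. The overweight/obese class can contain only GDM women, while the normal-weight class contains all the controls plus the leaner GDM women. A difference between the classes could therefore reflect GDM, BMI or both, and the contrast as written cannot tell them apart.

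**Working it through.** **The plan's own figure.** The sample of 40 (20 per group) is said to rest on earlier EEG studies. No power calculation is given, so there is none to reproduce.

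**Inputs from the document.** 20 GDM women; 20 controls, all with prepregnancy BMI below 25; a two-class test of weight; prepregnancy BMI available as a number.

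**Inputs assumed.** Two-sided alpha of 5%; a cut at 25; a correlation r between BMI and a single scalar brain-response measure; for the within-GDM check, BMI = 18 + a gamma variable with mean/SD of 25/4, 27/5.5 or 29/6.

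**Step 1: information kept by a cut.** For a linear relation and normally distributed BMI, classing multiplies the correlation by φ(z_p)/√(p(1−p)), where p is the share above the cut. Information kept is the square of that factor.
- p = 20/40: 0.399/0.5 = 0.798; squared, 0.64; 0.64 × 40 ≈ 25 women.
- p = 10/40: 0.318/0.433 = 0.734; squared, 0.54; 0.54 × 40 ≈ 21 women.

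**Step 2: power within the 20 GDM women, linear relation.** Simulation of response = r × standardised BMI + noise with variance 1 − r². The t-test on BMI ≥25 versus <25 is compared with the regression test on the same data. Ranges run over the three BMI distributions.

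| r | Cut at 25 | Continuous BMI | Difference (points) |
|---|---|---|---|
| 0.2 | 8–10% | 13–14% | about 3 to 6 |
| 0.4 | 18–27% | 42% | about 15 to 24 |
| 0.5 | 27–42% | 62–65% | about 20 to 38 |

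The differences are taken from the ends of the ranges, for example 42 − 27 = 15 and 42 − 18 = 24.

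**Step 3: all 40 women, GDM status in the model.** Assumed: controls with mean about 22 and SD 1.8, all below 25; GDM women with mean 27 and SD 5.5. A slope of 0.10 residual SD per kg/m2 gives about 37% with the cut and 65% with continuous BMI.

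**Step 4: a relation that is not linear.** If the response jumps at exactly 25, the ordering reverses: at r=0.5 within GDM women, the cut has 65–67% and continuous BMI 31–44%.

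**Step 5: mixing with GDM.** Let k of the 20 GDM women be overweight or obese. The overweight class is k women, all with GDM. The other class is 40 − k women, of whom 20 − k have GDM. If GDM shifts the brain response by δ and BMI has no effect at all, the expected difference between weight classes is

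δ × [1 − (20 − k)/(40 − k)] = δ × 20/(40 − k).

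- k = 8: 20/32 = 0.63δ.
- k = 14: 20/26 = 0.77δ.
- k = 20: 20/20 = δ, and the weight contrast is identical to the GDM contrast.

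The values of k are assumed. The direction does not depend on them: at least half of any GDM effect appears in the weight contrast.

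**The case against.** Four points can fairly be made for the plan.

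First, continuous body-size analysis is already planned. The regressions name weight and body fat, and the list is open. This stands in part: it lessens the loss to the study. But weight at the pregnancy visit is pregnant weight at 24–36 weeks, not prepregnancy BMI, and the regressions do not withdraw the two-class test. A reader might infer that the study as a whole loses the power shown above. The documents do not support that. The figures concern one contrast, under assumed inputs.

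Second, the sign of the effect depends on the shape of the relation, which the documents do not state. This stands. A step at 25 favours the cut. If the relation flattens above 27.5 (r=0.5 within GDM women), the continuous test is about 6 to 7 points ahead at a mean BMI of 25, but about 7 to 8 behind at 27 and 15 to 17 behind at 29. Nothing in the documents points to a step or a plateau, but nothing excludes them, so a linearity check is needed.

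Third, the analyses are exploratory, no power target is set, and weight class is not among the listed objectives. This limits the seriousness. It does not make the two-class test a better choice.

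Fourth, the contrast mirrors the fMRI evidence in the Introduction, which compares overweight and obese with normal-weight participants, and topography is easier to show by group. That supports keeping the classes as description.

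A reader might also infer residual confounding from BMI being classed when used as an adjuster. The plan does not say that it is classed there, so that reading has no basis.

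**Conclusion.** The point holds for this one contrast. The plan tests two weight classes where continuous prepregnancy BMI is available, and the eligibility rules place every overweight or obese woman in the GDM group.

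The mixing with GDM follows from the document alone. The loss of power does not: it rests on a roughly linear relation, a cut at 25 inferred from the control criterion, an assumed BMI distribution and a single scalar outcome. Under those assumptions it is small at r=0.2 (about 3 to 6 points within GDM women) and substantial at r=0.4 to 0.5 (about 15 to 38 points). No single range can be quoted as a property of the plan, because it states neither an effect size nor a BMI distribution.

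This is a cheap improvement to an exploratory analysis. It does not undermine the primary comparisons by visit and by GDM status.

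**What to change.** In the Statistical analysis plan section, replace the two-class weight test with a regression of the brain response on continuous prepregnancy BMI (kg/m2), fitted either in all women with GDM status in the model or within GDM women only. Continuous BMI in the pooled sample without GDM status would not remove the mixing. Report the slope per 5 kg/m2 with its 95% CI, and check linearity with a plot or one quadratic term. Keep the two-class comparison, including topography, as descriptive, and state the BMI cut-off that defines the classes.

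The change is wording only: no new data, visits or participants. The downside is the approximate-linearity assumption, which the check and the descriptive class results partly cover.

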## Ethics and dissemination

The local ethical committee approved the study protocol (study number 2021-01976). The study poses little to no risk to participants. Signed informed consent will be obtained from all participating women. The results of the study will be disseminated through national and international conferences, in peer-reviewed journals and presented at public conferences and other scientific meetings.

### Significance and outlook

The prevalence of obesity continues to increase worldwide. This study seeks to understand brain reactions to the viewing of food images and their changes during pregnancy and in the post partum period. Food cravings and disordered eating behaviours include implicit processes in the brain. Studying these processes could help unravel mechanistic pathways associated with weight gain. Our study may provide novel evidence of scientific and clinical importance to understand eating behaviour, potentially opening perspectives for future interventions that alter reactions to energy-dense food in general or at specific food nutrients and/or brain regions to manage excessive GWG, weight retention, and to reduce adverse metabolic outcomes in the post partum period. It is a potential opportunity to reduce craving, incentive sensitisation and thus the overstimulation of reward circuits by food cues in pregnant and post partum states where a dynamic change in craving and weight gain is observed. The study aims to provide data for a better understanding and long-lasting interventions that can influence the health of the mother and the child.
